**Figure 2 figure2:**
[figure not shown]
Timeline of participant involvement and measures.

#### Accessing Kirabo

Twice per week over the 5-week study period, Kirabo will send enrolled adolescents an SMS text message encouraging them to interact with our system. As noted earlier in the pretest, adolescents in the RCT can access Kirabo by sending the SMS text message “Hi” to #161 to initiate an interaction with Kirabo in English or Luganda. In the pretest, adolescents did not report any conflict with parents or school staff regarding their use of a mobile phone to interact with Kirabo.

### Measures

#### Overview

To evaluate the intervention’s impact, there will be 3 main assessment time points: baseline, immediately after the intervention, and 3-month follow-up. Table 2 provides a full list of measures. The primary outcome will be self-reported HIV testing, confirmed by HIV clinic records when possible. We will also measure the uptake of HIV prevention strategies (PrEP uptake and condom use) and, although we expect this to be a rare occurrence, the initiation of antiretroviral treatment. For adolescents who screen positive for behavioral health problems, we will confirm self-reports of linking to mental health care with a StrongMinds counselor.

Many of the measures have already been used, pretested, and made culturally appropriate to the Ugandan context in past studies [92,93], including current HIV prevention strategies and HIV-related knowledge. New measures, such as PrEP knowledge, will be adjusted according to the established ICHAD procedures. Specifically, to assess the uptake of HIV prevention strategies, we will compare presurvey and postsurvey scores from the current HIV prevention strategy measures that have been previously used in this region of Uganda with adolescents (Table 2) [72,73]. For questions measuring sensitive behaviors (ie, sexual risks), we will use audio computer-assisted self-interviews so that the participants may take the survey themselves on a minilaptop.

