**Behavioral, mental health, and alcohol use measures**			
	Demographics	Items developed for previous Suubi studies [72-74], including age, sex, parents’ occupation, household size, orphanhood status, primary caregiver, and community of origin	Baseline
	COVID-19 experiences	CASPE^a^ (adapted from Suubi+Adherence [74] and the study by Ladouceur [75])	Baseline
	HIV testing	Self-report of HIV test (yes/no; past year [at baseline], during the study period [immediately after the intervention], and past 3 months [at follow-up]) confirmed with proof of results from the clinic using measures and procedures adapted from Suubi studies [72-74]	Baseline, immediately after the intervention, and 3-month follow-up
	Intention to test for HIV	Questions adapted from a study of secondary school students in Uganda [76]	Baseline, immediately after the intervention, and 3-month follow-up
	Self-efficacy	Questions adapted from a study with secondary school students in Uganda [76] and a study with high school students in the United States [77], including questions regarding self-efficacy in testing for HIV, trying PrEP^b^, using condoms consistently, contacting a behavioral health counselor	Baseline, immediately after the intervention, and 3-month follow-up
	Current HIV prevention strategies	This measure includes items developed for previous Suubi studies [72,73] in Uganda (in addition to a question regarding PrEP; range 5-25; 5 question items; α=.70), for example, “I think it is very important to use condoms every time one has sex,” “as a teenager I think AIDS is a threat to my health,” and “I think all people my age who have sex should use condoms.” Scores range from 4: strongly agree; 3: somewhat agree; 2: somewhat disagree; to 1: strongly disagree.	Baseline, immediately after the intervention, and 3-month follow-up
	HIV-related knowledge	This measure includes items from previous Suubi studies [72,73] in Uganda; this measure includes 13 items about HIV infection and prevention mechanisms (range 0-16; 16 question items; α=.83), for example, “HIV can be passed by an infected person even though that person is not feeling sick.” Possible scores are 1: true; 2: false; and 3: don't know or 1: not sure; 2: unsafe; and 3: safe.	Baseline, immediately after the intervention, and 3-month follow-up

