### Phases 7 to 8: Training and RCT Pilot Study

#### Procedures

We plan to conduct a 2-arm, randomized controlled study via mobile phones among adolescents in the greater Masaka region of Uganda. We will compare Kirabo to an inactive control and evaluate whether adolescents who interacted with Kirabo had higher rates of self-reported HIV testing (yes/no; verified with the HIV clinic when possible) immediately after the intervention and at the 3-month follow-up assessment. Secondary outcomes include differences in condom use, PrEP knowledge, PrEP uptake for eligible patients, HIV-related knowledge and sexual risk behaviors, and antiretroviral treatment uptake for eligible patients. Exploratory aims include the number of participants who screen positive for symptoms of depression, anxiety, and hazardous alcohol use and the proportion of confirmed linkages to mental health counseling.

Adolescents (aged 15-19 years) in the greater Masaka region in southern Uganda who own a mobile phone will be eligible for the trial. Adolescents will be involved in the trial for approximately 5 weeks with a 3-month follow-up assessment (Figure 2). After informed assent and parental permission, the baseline assessment, and confirmation of eligibility, adolescents will be randomly assigned to the Kirabo intervention group or standard of care group. Randomization will be performed in a 1:1 ratio and stratified by gender and school (to minimize contamination) with a block size of 10. We anticipate recruiting students from 20 schools. The treatment assignments will be generated using a pseudorandom number generator. An electronic list of IDs, access codes, and credentials will be provided securely to the sites.

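### Condom use and PrEP uptake are declared as behavioural outcomes, but the scale named to assess them is printed with an agreement format and opinion items

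*Protocol article*

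**What the plan says.** Under Procedures (Phases 7 to 8), the article states: "Secondary outcomes include differences in condom use, PrEP knowledge, PrEP uptake for eligible patients". The Measures overview treats the same two behaviours as what uptake means: "We will also measure the uptake of HIV prevention strategies (PrEP uptake and condom use". It then names the instrument: "to assess the uptake of HIV prevention strategies, we will compare presurvey and postsurvey scores from the current HIV prevention strategy measures".

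Table 2 describes that instrument in the row for current HIV prevention strategies. It gives three example items. One is an opinion on the importance of condoms: "I think it is very important to use condoms every time one has sex". Another records perceived threat: "as a teenager I think AIDS is a threat to my health". The third is a norm for peers: "I think all people my age who have sex should use condoms". The response format is "Scores range from 4: strongly agree; 3: somewhat agree; 2: somewhat disagree; to 1: strongly disagree", and the scale is summarised as "range 5-25; 5 question items; α=.70". The row mentions an additional PrEP question without its wording or its own response format. The measure is scheduled at baseline, immediately after the intervention and at 3 months.

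**The concern.** Condom use and PrEP uptake are things a participant does. The printed items record what a participant thinks. If the scale score is the evidence for uptake, a rise in agreement that condoms matter would be reported as a rise in use of prevention.

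The risk is specific to this intervention. The section on the IMB model places perceived risk and peer norms among the motivational factors that the messages may enhance, and treats PrEP uptake as a behaviour they influence. The example items resemble those factors. A real, randomised difference between arms on this score could therefore be an effect on a hypothesised mediator, reported under the name of the outcome. The Limitations section says the pilot's data will be the basis for a larger trial, so the label could carry into that trial's planning.

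**Working it through.** The article gives no figure for the uptake outcomes that could be reproduced. The check is a comparison of sections, plus the score range in Table 2.

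**1. Outcome against instrument**

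| Element | Where | Content |
|---|---|---|
| Outcome | Procedures; Measures, Overview | Condom use; PrEP uptake among eligible participants |
| Named instrument | Measures, Overview | Scores on the current HIV prevention strategies measure |
| Items shown | Table 2, that row | Importance of condoms; AIDS as a threat; whether peers should use condoms |
| Response format | Table 2, that row | Four levels of agreement |

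None of the three items shown asks whether the respondent used a condom or started PrEP. A summed score also has no eligible-participant denominator, which the PrEP outcome requires.

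**2. Is the behaviour recorded elsewhere?** The Measures overview presents Table 2 as the complete list. The nearest rows are:
- self-efficacy, which is confidence about trying PrEP and using condoms;
- PrEP knowledge, which is true-false items;
- sexual risk behaviors, which has never-to-always anchors but a belief as its one example item, and is not named as the uptake measure.

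No row is labelled as recording condom use or PrEP initiation. The HIV testing row, by contrast, gives a yes/no answer, a recall period for each visit and clinic proof, so the same table shows what a behavioural definition looks like.

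**3. What a change in opinion does to the score.** On the printed coding, suppose a respondent moves from somewhat agree (3) to strongly agree (4):
- on the three items shown: 3 × 3 = 9 to 3 × 4 = 12, a rise of 3 points;
- on all five, assuming the two unseen items are of the same kind: 5 × 3 = 15 to 5 × 4 = 20, a rise of 5 points.

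Neither rise needs any change in behaviour.

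**4. Score range.** Range = items × lowest code to items × highest code.
- Five items coded 1 to 4: 5 × 1 = 5 to 5 × 4 = 20.
- Six items (with the PrEP question) coded 1 to 4: 6 × 1 = 6 to 6 × 4 = 24.
- Printed: 5 to 25. Five items reach 25 only with five response levels (5 × 5 = 25).

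Either the range or the response coding is misprinted. The article does not show which.

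**The case against.** The strongest reply is that the instrument is only partly visible. Three items are introduced as examples out of five, and the PrEP question may ask about actual use or stand apart from the summed scale. An article also commonly leaves item wording to the full protocol, and antiretroviral initiation is promised although Table 2 has no row for it, so a missing row does not prove that no item exists. This stands as a limit on certainty, especially for PrEP. It does not remove the point: the article does not stay silent on how uptake is assessed but names the instrument and its scores, and what is printed about that instrument is attitudinal.

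The printed response coding may itself be the misprint, since 5 to 25 fits five levels. That is fair, but the three items are opinions under either coding.

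Three stronger readings are tempting and are not supported:
- **An uncontrolled before-after comparison.** A reader might infer this from the mention of presurvey and postsurvey scores. Primary and Secondary Outcomes and Analysis extends the mixed model, with assignment as main predictor, to the secondary outcomes, so the between-arm contrast is in place.
- **The same flaw for antiretroviral uptake.** The Measures overview names antiretroviral initiation separately from prevention strategies and does not tie it to this scale.
- **That someone who has never used a condom or PrEP can score the maximum.** This is true of the three items shown, but cannot be asserted for the whole scale while the other items are unseen.

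Finally, these are secondary outcomes in a pilot whose stated main purpose is acceptability and feasibility. The HIV testing outcome is a behaviour, checked against clinic records when possible, and is unaffected. That limits the weight of the point.

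**Conclusion.** The concern holds in a bounded form. Two declared behavioural outcomes are tied to a score that, as printed, reflects attitudes and perceived threat, so a between-arm difference in attitude could be reported as uptake. For condom use this follows from the items shown, on the assumption that they represent the scale. For PrEP it is conditional on the added question: even if that question asks about use, the plan compares scores on the measure and does not name the item as an outcome of its own.

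The size of the effect on any conclusion cannot be computed from the article. The range discrepancy can: the printed maximum of 25 exceeds the five-item maximum by 5 points and the six-item maximum by 1 point, and the printed minimum of 5 is 1 below the six-item minimum. This should be corrected before the uptake outcomes are analysed and reported. It does not touch the primary outcome.

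**What to change.** In the Measures overview and Table 2:
- Define condom use as a separate behaviour item with a recall period and sexually active participants as the denominator.
- Define PrEP uptake as a separate yes/no item among eligible participants.
- Place both items in the audio computer-assisted self-interview already planned for sensitive behaviours, in both arms at the visits already scheduled for this measure.
- State that both are analysed with the between-arm mixed model already specified for secondary outcomes.
- Report the agreement scale as attitudes only, and remove the statement that its scores assess uptake.
- Reconcile the scale's range with its number of items and response coding, and say whether the PrEP question counts towards the sum.

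If the full questionnaire already contains such behaviour items, naming them as the outcome measures is enough and only wording changes. Otherwise the cost is a slightly longer questionnaire. No new visits or analysis model are needed. If data collection has already passed the relevant visits, the items cannot be recovered for those participants, and the scale result should then be reported as attitudes and not as uptake.

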#### Behavioral Health Screeners via Mobile Phone

As in the pretest, behavioral health screeners will be delivered via adolescents’ mobile phones and automatically scored by Kirabo. In addition, we will use the same measures of behavioral health in the baseline and 3-month follow-up battery.

#### Acceptability and Feasibility Measures

All adolescents in the intervention will complete the 15-item acceptability survey adapted from prior mental, sexual, and reproductive health work among adolescents in Uganda [94]. To further evaluate feasibility, we will use paradata and text count measures previously used by FHI 360 (Table 2) [54].

In addition to the quantitative measures included in Table 2, immediately after the intervention, we will conduct 30 key informant interviews (KIIs) with participants in the intervention group. The KII guide draws from the Consolidated Framework for Implementation Research (CFIR) [95,96], with a focus on the intervention characteristics and the outer setting, and will be adapted from our pretest KII guide. For example, through our pretest and subsequent focus groups, we identified the necessary changes to our intervention based on adolescents’ descriptions of outer-setting barriers. Specifically, adolescents reported that they often experienced intermittent mobile phone service. Our earlier version of the mobile phone intervention that included IVR required callers to restart at the initial message each time they called in. Adolescents in our focus groups expressed that restarting the IVR each time a call dropped was cumbersome and frustrating. By contrast, adolescents found that SMS text messaging could be resumed wherever they had left off when their service resumed. Adolescents overwhelmingly selected SMS text messaging as their preferred means of interacting with Kirabo. Acceptability questions will probe adolescents’ comfort with content and delivery methods. All adolescents in the intervention will complete the 15-item acceptability survey adapted from prior mental, sexual, and reproductive health work among adolescents in Uganda [94]. To further evaluate feasibility, we will use paradata and text count measures previously used by FHI 360 (Table 2) [54].

### Statistical Analysis

#### Primary and Secondary Outcomes and Analysis

Summary statistics will be used to describe all metrics and compare them between the students receiving Kirabo and those in usual care at baseline, 1-month postintervention assessment, and the final 3-month follow-up assessment. Means and SDs will be used for continuous outcomes, followed by box plots, and frequency tables will be used for binary and categorical metrics. The primary analysis of this RCT will test whether postintervention HIV testing rates among the adolescents who interacted with Kirabo are significantly higher than those who received standard of care. We will use a generalized linear mixed model to determine statistical significance. In the model, the outcome is the binary indicator of whether an adolescent received an HIV test during or immediately after the intervention. We will also examine the differences between the model at the 3-month follow-up. The main predictor is the intervention assignment (Kirabo or usual care). The school will be included in the model as the random effect to adjust for within-school correlations. We will apply similar analyses to investigate the impact of Kirabo on the secondary outcomes.

Depending on the nature of the outcome, we will use different link functions in the generalized linear mixed model. We will use the identity link for continuous outcomes, the logistic link for binary outcomes, and the log function for ordinal outcomes. For incidence/frequency outcomes, a log function with adjustment for exposure time will be used. We will formally test whether the students in the 2 intervention groups have comparable baseline characteristics, including demographic factors, moderators, and variables measuring potential mechanisms of action (Table 2). If any of these variables are significantly different at baseline, they will be included in the model to adjust for their potential confounding effects.

#### Acceptability Power Analyses

The primary purpose of this pilot RCT is to determine whether Kirabo is acceptable (>70% of adolescents “agree” or “completely agree” with 70% of acceptability measure items) and feasible (enrollment >75%) in this setting. The 100 participants in the Kirabo arm will provide 80% power to detect the proportion of participants who meet the acceptability agreement threshold as significantly greater than 70% if the observed proportion of participants who meet this threshold is at least 83.5%.

#### Effectiveness Power Analysis

There is limited information on the impact of SMS text message–based interventions on increasing HIV testing among adolescents in rural Uganda. We expect that the baseline 12-month HIV testing rate among adolescents aged 15 to 19 years will be 26% [97]. With 200 students (intervention: n=100, 50%; standard of care: n=100, 50%) from 10 schools, we have 80% power to detect an average postintervention HIV test rate of ≥46% at the significance level of.05.

#### Handling of Missing Data

If more than 10% of the observations are missing, we will use multiple imputation strategy to accommodate missing data, followed by sensitivity analysis. The inclusion of cases with partial data is an important step because the intention-to-treat approach is planned to be the main analytic strategy for the primary aim of generating preliminary estimates of Kirabo’s efficacy. If the statistical or clinical significance of treatment effects appears to differ depending on how missing data are addressed in the analyses, such findings will be reported.

#### Primary End Point Analysis for the Pilot RCT

We will recruit 200 students who own mobile phones and randomize them in a 1:1 ratio into intervention and control groups. The variables of focus are listed in Table 2. The primary end point is the binary indicator of whether there is an increase in HIV testing following the intervention. Chi-square tests will be used to determine whether intervention participants were more likely to take an HIV test in the past month. We will then build a logistic model to estimate intervention efficiency while adjusting for baseline characteristics, including baseline HIV prevention strategies, HIV knowledge, sexual risk behaviors, depression, anxiety, alcohol use, and demographics. The same analysis will be applied to the 6-month postintervention follow-up to determine the long-term effects of the intervention. These estimated parameters allow reliable estimates of sample size, power, and detectable effects for the subsequent study.

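### The primary end point is worded as an increase in HIV testing in one section and as tested yes/no elsewhere; the plan should fix one definition and one recall window

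*Protocol article*

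**What the plan says.** The protocol article describes the primary HIV-testing variable in several places.

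- Primary End Point Analysis for the Pilot RCT: "The primary end point is the binary indicator of whether there is an increase in HIV testing following the intervention". The next sentence reads: "Chi-square tests will be used to determine whether intervention participants were more likely to take an HIV test in the past month". A logistic model adjusted for baseline characteristics follows.
- Primary and Secondary Outcomes and Analysis: in the generalized linear mixed model, "the outcome is the binary indicator of whether an adolescent received an HIV test during or immediately after the intervention".
- Measures, Overview: "The primary outcome will be self-reported HIV testing, confirmed by HIV clinic records when possible".
- Table 2, HIV testing row: a yes/no item whose recall windows are "past year [at baseline], during the study period [immediately after the intervention], and past 3 months [at follow-up"].
- Effectiveness Power Analysis: "We expect that the baseline 12-month HIV testing rate among adolescents aged 15 to 19 years will be 26"%, and "we have 80% power to detect an average postintervention HIV test rate of ≥46% at the significance level of.05". The sample is given as "With 200 students (intervention: n=100, 50%; standard of care: n=100, 50%) from 10 schools".

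Procedures puts participants' involvement at about 5 weeks, followed by a 3-month follow-up assessment.

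**The concern.** The sentence that formally names the primary end point describes a change. The model, the Measures section and the power statement describe a state: tested or not. These are different variables and can give different rates and a different treatment effect.

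The participant-level reading is not far-fetched. A binary indicator entered into a chi-square test and a logistic model needs one value per adolescent. Built from the Table 2 items, it would have two faults:

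- An adolescent who is already a yes at baseline cannot go up, so someone who tested in the prior year and tests again during the intervention would be scored as a failure.
- The baseline item covers 12 months and the post-intervention item about 5 weeks, so the difference is not a change in testing rate.

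At stake are which variable is analysed as primary, whether it is the one that was powered, and the estimates the section says will be used to size the next study. With more than one wording in the plan, the choice could also be made after the data are seen.

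**Working it through.** **1. Definitions side by side**

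| Section | Variable | Window |
|---|---|---|
| Measures, Overview | tested, self-reported | none given |
| Table 2 | tested yes/no | past year at baseline; study period after the intervention |
| Primary and Secondary Outcomes | tested yes/no | during or immediately after the intervention |
| Effectiveness Power Analysis | testing rate, 26% vs 46% | 12 months for the 26% |
| Primary End Point Analysis, end-point sentence | increase in testing | none given |
| Primary End Point Analysis, next sentence | tested | past month |

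Only one entry is a change. The past-month window also fits neither of the others: 5 weeks is 35 days, so a month taken as 30 days leaves about the first 5 days of the study period uncovered.

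**2. Reproducing the stated power**

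Inputs from Effectiveness Power Analysis: 100 per arm, 26% vs 46%, significance level 0.05. Sidedness is not stated; two-sided is assumed here and throughout. School clustering is ignored.

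- Fisher's exact test, all binomial outcomes enumerated: 80.4%.
- Chi-square with continuity correction: 80.4%.
- Uncorrected chi-square, normal approximation: 84.3%.

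The stated 80% is reproduced, and it belongs to the plain tested yes/no outcome.

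**3. If *increase* were coded per participant**

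Success = no test in the year before baseline and a test in the study period. Let b = 0.26 be the share with a prior-year test, p the overall post-intervention rate (0.26 or 0.46), and r the ratio of the chance of testing among prior-year testers to that among the others, taken as equal in both arms.

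- Chance of testing without a prior-year test: q = p / (0.74 + 0.26r)
- Success rate: 0.74 × q

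Under independence (r = 1), q = p, so the rates are 0.74 × 0.26 = 19.2% and 0.74 × 0.46 = 34.0%. The difference is 14.8 points instead of 20. Fisher power is 60.4% (uncorrected chi-square 66.0%). Reaching 80% would take about 139 per arm, or 153 with the continuity correction.

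Other values of r, which the documents do not give:

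| r | Control | Kirabo | Fisher power |
|---|---|---|---|
| 0 | 26.0% | 46.0% | 80.4% |
| 0.25 | 23.9% | 42.3% | 74.8% |
| 0.5 | 22.1% | 39.1% | 69.8% |
| 0.75 | 20.6% | 36.4% | 64.9% |
| 1 | 19.2% | 34.0% | 60.4% |
| 1.5 | 17.0% | 30.1% | 52.7% |
| 2 | 15.3% | 27.0% | 46.5% |
| 3 | 12.7% | 22.4% | 37.6% |

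**4. Sensitivity to how dependence is modelled**

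If instead the same correlation φ between baseline and later testing is assumed in both arms, success is p − [bp + φ√(b(1−b)p(1−p))]. For φ = 0.2, 0.3 and 0.5, Fisher power is 62.1%, 63.6% and 68.8%: it rises with dependence, whereas with a common ratio it falls. In the extreme where every control-arm tester is a prior-year tester (about 0% vs 20%), power is near 100%. No single power figure therefore follows from the documents.

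**The case against.** The best defence is that the section's own next sentence shows what is meant: it compares the arms on whether a test was taken, with no subtraction of baseline. Procedures, Measures, the mixed-model paragraph and the power statement agree. On that view *increase* is loose wording for the group-level hypothesis, and the unequal recall windows are a reason to doubt that a within-person change was ever planned. It can also be said that the stated primary purpose of this pilot is acceptability and feasibility, so an unclear efficacy end point weighs less than it would in a confirmatory trial.

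Most of this stands. A reader might infer from the end-point sentence that prior-year testers cannot count as successes and that, on the plan's own rates, power is only about 60% to 69%. The documents do not support that. No section bars prior-year testers from success, and any such power range needs a retest assumption found nowhere in the text. Under the tested yes/no outcome the stated 80% holds.

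The defence does not remove the conflict. A group-level increase cannot be the dependent variable in a chi-square test or logistic model, so the sentence naming the primary end point still does not identify the variable to be analysed. The sentence offered in its defence brings in yet another window.

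**Conclusion.** The end-point sentence is wrong as written, in a limited sense: it conflicts with the outcome that is measured, modelled and powered elsewhere, and with the sentence after it. The intended outcome is most likely tested yes/no, and on that outcome the power statement reproduces.

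The loss of power is conditional on coding the increase per participant. It is then about 20 percentage points (80.4% to 60.4%) if repeat testing is independent of earlier testing, and between none and about 43 points (80.4% to 37.6%) for a common retest ratio of 0 to 3. These figures also rest on a two-sided 5% Fisher test, no clustering, and the plan's use of a 12-month 26% as the control rate for a much shorter window. They show what the ambiguity could cost; they do not estimate the trial's actual power. The correction is worth making because it settles the primary variable at almost no cost.

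**What to change.** In Primary End Point Analysis for the Pilot RCT:

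1. Replace the end-point sentence with a single definition consistent with Table 2 and the mixed-model paragraph, for instance: the primary end point is whether the adolescent received an HIV test during the study period (yes/no), assessed immediately after the intervention.
2. Replace the past-month window in the chi-square sentence with that same study-period window.
3. State that no change-from-baseline indicator will be formed.
4. Add baseline past-year HIV testing to the covariates of the adjusted model. Table 2 already collects it, but the section's covariate list does not name it.

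The cost is a few lines of text, with no new data and no further participants. If the sponsor does mean a per-participant increase, the recall windows must be made comparable and the sample size redone under a stated retest assumption; under independence about 139 per arm would be needed (153 with continuity correction), against the planned 100.
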